### Concealment mechanism

All participants who provide consent for participation and who fulfil all eligibility criteria will be randomized. Participants will be randomized using the central web-based Research Electronic Data Capture (REDCap) [15] randomization module. A statistician not otherwise involved with the trial will generate the randomization sequence and upload it into the REDCap randomization module. The module sequentially assigns participants to treatment groups and monitors the progress of allocation. The randomization sequence and blocking information will be concealed from all trial staff including the principal investigator, the biostatistician, and trial coordinators until the database is closed.

### Implementation

The trial coordinator will enroll participants in the trial. Once a participant is enrolled, the trial coordinator will access REDCap to randomize participants to either VATS-Lobectomy or RTS-Lobectomy. After a participant has been randomized, the allocation information will be stored in the database and will not be able to be modified.

## Assignment of interventions: Blinding

### Who will be blinded

As this is a surgical trial, provider blinding will not be feasible. Participants will remain blinded to the type of surgery they receive from the time of enrollment until the end of the trial follow-up period, at which time the trial coordinator will inform the participant as to which intervention they were randomized to (VATS-Lobectomy or RTS-Lobectomy). The operating room setup and resulting scars from both surgical procedures are comparable and should not compromise participant blinding. The biostatistician performing the analysis will be blinded as to which intervention arm participants were allocated to as the group allocations will be coded as Group A and Group B. To reduce observer bias, the trial coordinator (outcome assessor) will only provide minimal assistance (e.g., reading a question) to participants while they are completing their self-reported Trial Health Questionnaire.

### Procedure for unblinding if needed

At the end of the trial follow-up period, the trial coordinator will inform the participant as to which intervention they were randomized to (VATS-Lobectomy or RTS-Lobectomy).

## Data collection and management

### Plans for assessment and collection of outcomes

#### Data collection

This trial will include baseline, hospital, and follow-up (weeks 3, 7, 12; months 6, 12, 18, 24; and years 3, 4, and 5) assessments. Data for the trial will be gathered from the participants, electronic health records, and surgeon’s office chart as well as hospital databases (e.g., costing database). In addition, participants will be asked to complete the Trial Health Questionnaires and a Study Diary. Fig 2 provides a summary of the schedule of assessments and evaluations being conducted.

#### Baseline data collection

Baseline data including demographics (e.g., age, BMI, gender), medical history (e.g., smoking, alcohol use, comorbidities, analgesia consumption, pain, previous thoracic surgery, previous cancer), tumour characteristics (e.g., clinical stage, histology), and physiology (e.g., pulmonary function) will be collected. In addition, participants will be asked to complete the Trial Health Questionnaire and they will be provided with a Study Diary.

#### Hospital stay data collection

Hospitalization data including hospital admission date, hospital discharge date, chest tube removal date, intraoperative blood loss, and postsurgical pain will be collected. During the hospital stay, the pain will be assessed with the Numeric Pain Rating Scale (NPRS) on movement (deep breathing or mobilization) and analgesic consumption will be collected daily starting with postoperative day 1, until the date of discharge, and the videotape of the surgery will be collected. Pathology details will be collected including the number of lymph nodes harvested, pathology stage and histology. Direct costing data will also be collected (e.g., equipment used, surgical disposables used, staff in operating room, number of days in step down or intensive care unit, medications used). In addition, prior to discharge, participants will be asked to complete the Trial Health Questionnaire.

#### Follow-up assessment data collection

At the 3-, 7-, 12-week, 6-, 18-month, and 1-, 2-, 3-, 4-, and 5-year trial follow-up assessments, participants will be asked to complete the Trial Health Questionnaire and review the Study Diary with the trial coordinator. This is estimated to require 15 minutes of time. Five-year survival data will also be obtained by conducting a quick chart review at five-years. The patients have routine surveillance follow-up appointments with the surgeon every 6 or 12 months after surgery, either in-person or virtually, so survival data will be available from the surgeon’s surveillance follow-up note at five-years. The only survival data that will be collected at five-years is the status of the patient at five years (alive or not).

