#### Secondary outcomes

To determine:

Short-term clinical outcome differences, the following will be collected: clinical staging, pathological staging, number of lymph nodes sampled, admission date, date of surgery, discharge date, chest tube removal date, intraoperative blood loss, post-operative analgesia, and post-surgical pain.Resource utilization, a healthcare resource utilization tracking system will be developed for the specific purpose of the trial in order to allow for an accurate cost analysis. Variables that will be tracked include utilization of operating room time, operating room staff, surgical instruments and consumables, admission to critical care beds, hospital length of stay, duration of intravenous analgesia, postoperative complications, and costs associated with chronic post-surgical pain up to one year after surgery.Cost-Effectiveness, the incremental cost per quality-adjusted life year (QALY) gained will be calculated.Differences in HRQOL scores between the treatment groups, the EQ-5D-5L questionnaire will be administered at weeks 3 and 7; months 6, 12, 18, 24; and years 3, 4, and 5, which coincide with the intervals of oncological surveillance.Overall survival, the difference in 5-year survival rate between the two groups will be calculated.

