#### Follow-up assessment

Follow-up will occur at weeks 3, 7, and 12; then months 6, 12, 18, and 24; and then years 3, 4, and 5 from the date of hospital discharge. All follow-up assessments, except for the 7-week, will take place in the hospital clinic at the time of the participant’s routine follow-up visits with the surgeon. The trial coordinator will be available to assist the participant in completion of the Trial Health Questionnaire as well as review the Study Diary with the participant. At the 7-week trial follow-up assessment, the trial coordinator will collect the data over the telephone. Five-year survival data will also be obtained by conducting a quick chart review at five-years. The patients have routine surveillance follow-up appointments with the surgeon every 6 or 12 months after surgery, either in-person or virtually, so survival data will be available from the surgeon’s surveillance follow-up note at five years.

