#### Secondary outcome in Phase B

Differences in QALY will require a higher number of measurements to be detected. Overall survival at 5-years will also require a larger sample size over a longer period of observation. These secondary outcomes of interest require the trial to be repowered so that they can be adequately powered. Based on a hypothesized 10% 5-year survival difference between the control arm and the experimental arm, the estimated sample sizes for two-sample comparison of survivor functions using the Log-rank test Freedman method with 80% power at a level of significance of 0.05 is 592 patients, with 296 patients per arm. A drop-out rate is not factored into this analysis since the Freedman method of censoring was employed, accounting for loss of patients over time. Also, an assumption for Stage I patients was made during this sample size calculation, since the majority of patients who are operated on are Stage I. Also, this calculation is not a non-inferiority design. This larger, sufficient sample size will allow comparison of difference in overall cost-effectiveness and survival.

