## Statistical methods

### Statistical methods for primary and secondary outcomes

Baseline characteristics of both treatment groups will be compared to ensure homogeneity in the patient population. Descriptive statistics will be reported by treatment group where categorical variables will be reported as counts (percentages) and continuous variables as mean (standard deviation) or as median (25^th^ percentile, 75th percentile). All analyses of primary and secondary outcomes will be carried out based on the intention-to-treat principle. Unadjusted comparisons of continuous outcome measures will be carried out using an independent t-test or the Wilcoxon rank-sum test if the assumptions of the t-test were violated. Unadjusted comparisons of categorical outcome measures will be computed using the chi-squared test, or the Fisher’s exact test if any of the expected values in the contingency table is less than 5, or McNemar’s test. For adjusted analyses, multivariable logistic regression analyses will be used for binary outcomes and multivariable linear regression for continuous outcomes. The results of comparisons between groups will be presented as mean differences for continuous outcomes and relative risks or odds ratios for binary outcomes, with corresponding 95% confidence intervals and associated p-values. ANOVA will be used for repeated measures. Survival will be compared using the Kaplan-Meier method and cox proportional hazard models. Survival curves will be compared using the Log-rank test. P-values will be reported to three decimal places with p-values less than 0.001 reported as p < 0.001. All analyses will be performed using SAS. Table 3 provides a summary of the variables, measures and methods of analysis.

**Table 3 pone.0261767.t003:** Variables, measures and methods of analysis.

Variable/Outcome	Hypothesis*	Outcome	Method of Analysis

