○ The cost analysis will only involve aspects of intraoperative and postoperative care because the preoperative evaluation of patients in both groups is identical. For robotic costs, calculating depreciation and maintenance costs for robotic equipment, based on the percent utilization of robotic resources by the thoracic surgery service will be done. Total costs will be calculated using the natural units of the relevant health care resource used by each participant and the unit costs for each resource item. QALY will be calculated by the area under the curve method, using health utility measured by EQ-5D-5L and the corresponding time duration. The incremental cost per QALY gained is calculated using the difference in the total cost divided by the difference in mean QALYs between RTS- and VATS-Lobectomy. Sampling uncertainty will be handled using the nonparametric bootstrapping approach. Cost effectiveness curves will be used to calculate the probability of RTS-Lobectomy being more cost effective than VATS-Lobectomy in treating this patient population at a wide range of maximum willingness to pay thresholds.HRQOL
○ The HRQOL will be analyzed as per the primary outcome at weeks 3 and 7, and months 6 and 18, and 1-, 2-, 3-, 4- and 5-years.Survival Analysis
○ Time to event analysis models will be used to compare overall survival at 3 years and 5 years between trial arms.

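### Phase B plans time-to-event survival analyses and a 3-year comparison, but the survival data specified are a single alive-or-not status at five years, which cannot support them

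*Protocol article*

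**What the plan says.** **Data collection.** Under Follow-up assessment, "Five-year survival data will also be obtained by conducting a quick chart review at five-years". The named source is the surgeon's surveillance note at five years. Follow-up assessment data collection repeats this and ends: "The only survival data that will be collected at five-years is the status of the patient at five years (alive or not").

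**Analysis.** Under Statistical methods for primary and secondary outcomes, "Survival will be compared using the Kaplan-Meier method and cox proportional hazard models", and "Survival curves will be compared using the Log-rank test". Table 3 lists the same methods for overall survival. Under Secondary analysis, "Time to event analysis models will be used to compare overall survival at 3 years and 5 years between trial arms". The Secondary outcomes section describes a single time point: "Overall survival, the difference in 5-year survival rate between the two groups will be calculated".

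**Sample size.** Secondary outcome in Phase B starts from this premise: "Based on a hypothesized 10% 5-year survival difference between the control arm and the experimental arm". The result is "Log-rank test Freedman method with 80% power at a level of significance of 0.05 is 592 patients, with 296 patients per arm". That section adds no drop-out allowance, on the ground that the method's censoring covers patients lost over time. It mentions a Stage I assumption but gives no control-arm survival rate.

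**The concern.** Kaplan-Meier, log-rank and Cox analyses need, for each patient, either a date of death or a date last known alive. One binary status at five years supplies neither. It does not order the deaths, it gives no follow-up time for a patient who leaves care, and it says nothing about who was alive at three years. The source adds to the problem, because a patient who died in year 2 or moved to another hospital would not be expected to have a five-year note from the surgeon.

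At stake are the log-rank test on which the 592 rests, the hazard ratio, the survival curves and the 3-year comparison. The reason for adding no drop-out allowance is also affected, since censoring can absorb losses only if censoring times are recorded.

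**Working it through.** **1. What each planned output needs, and what is specified**

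| Planned output | Needs | In the survival data specified? |
|---|---|---|
| Kaplan-Meier curves | death and censoring times | no |
| Log-rank test | ordered death and censoring times | no |
| Cox model | the same | no |
| 3-year comparison | status or time at 3 years | no |
| Difference in 5-year rate | status at 5 years for everyone | yes, if complete |

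The article does name dates where it wants them: admission, surgery, discharge, chest tube removal and withdrawal. It does not name date of death, date last known alive or 3-year vital status.

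**2. The plan's own figure**

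Inputs stated: 10-point difference at 5 years, 80% power, significance level 0.05, 1:1 allocation, Freedman method. Assumed: two-sided test, control survival 70% (so 70% versus 80%).

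- HR = ln(0.80)/ln(0.70) = 0.626
- Events = (1.960 + 0.842)² × [(1 + 0.626)/(1 − 0.626)]² ≈ 148
- N = 2 × 148/(2 − 0.70 − 0.80) = 592

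This matches the stated 592. The back-solved control rate is a guess: on the same formula 65% versus 75% gives 660 and 75% versus 85% gives 508, while a one-sided test with control survival of 40% to 55% gives 585 to 599.

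**3. What status alone would deliver (two proportions, 70% versus 80%)**

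- n per arm = [1.960√(2 × 0.75 × 0.25) + 0.842√(0.70 × 0.30 + 0.80 × 0.20)]²/0.10² = 293.2, so 294 per arm or 588 in total.
- Power with 296 per arm, by assumed share of unknown statuses:

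| Unknown | 0% | 5% | 10% | 15% | 20% |
|---|---|---|---|---|---|
| Power | 80.4% | 78.3% | 76.1% | 73.7% | 71.1% |

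A log-rank test also loses power to censoring, so these falls are not all due to the missing dates. In a simulation of 600 trials at an assumed 68% versus 78%, with about 8% of statuses unknown, the log-rank test on exact times had 76% power and the comparison of known statuses 75%.

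**4. Bias if unknown statuses are dropped (assumed rates, true 70% versus 80%)**

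- 10% of survivors missing in both arms: 0.63/0.93 = 67.7% versus 0.72/0.92 = 78.3%, difference 10.5 points.
- 25% of deaths missing in both arms: 0.70/0.925 = 75.7% versus 0.80/0.95 = 84.2%, difference 8.5 points.
- 25% of deaths missing in one arm only: 84.2 − 70.0 = 14.2 points if only in the better arm, or 80.0 − 75.7 = 4.3 points if only in the other.

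**The case against.** The strongest reply is that the restrictive sentence covers only what is collected at five years. The chart review is described as an addition to scheduled contact at weeks 3, 7 and 12, months 6, 12, 18 and 24, and years 3, 4 and 5. Adverse events are collected from consent to the end of follow-up, withdrawals are dated, and missed visits prompt telephone attempts. Deaths reported as serious adverse events and visits attended could supply many event times, at worst within an interval, as well as censoring points and much of the 3-year status.

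This stands in part. A reader might infer that every survival output is bound to fail and that patients without a five-year note can only be dropped. The documents do not support that. What remains is that none of these records is designated as a source of survival data, no rule says how to turn them into times, and a missed visit does not date a death.

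A second reply is that an article condenses the full protocol, and that the schedule figure and case report form are not shown. That would answer a mere silence. Here the article makes a positive statement, with the word only, that conflicts with its own analysis section. A later analysis plan can choose a model, but it cannot supply dates that were never collected.

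Third, overall survival is a secondary outcome described as a difference in 5-year rate, which complete status can estimate. This is correct. It does not rescue the log-rank test, the Cox model or the 3-year comparison. The Phase A primary outcome is unaffected, and Phase B also serves cost-effectiveness and longer-term quality of life.

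**Conclusion.** The point holds as a conflict between data collection and analysis: the time-to-event analyses and the 3-year comparison cannot be run from the survival data the protocol says it will collect. The stated ground for omitting a drop-out allowance has the same weakness.

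Two stronger inferences should be resisted. The sample size is not shown to be wrong: 592 reproduces under a plausible assumption, and complete 5-year status would give nearly the same power (80.4%) for a comparison of proportions. Nor is serious bias shown. With the assumed losses equal in both arms, the difference moves from 10 points to 10.5 or 8.5. Larger bias needs missingness that differs by arm, and the documents give no reason to expect that.

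The power and bias figures rest on the assumed 70% versus 80%, a two-sided test and assumed rates of unknown status. The conflict between the sections rests on none of them.

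**What to change.** - Replace the restrictive sentence under Follow-up assessment data collection. At every follow-up and at the 5-year chart review, record vital status, date of death and, for anyone not known to have died, date last known alive.
- Where there is no 5-year note, use the last chart contact or the serious adverse event record, and name these as survival sources.
- Define overall survival as time from randomization, in line with intention-to-treat, censored at the date last known alive. The follow-up schedule runs from hospital discharge, so the time origin needs stating.
- Align the wording under Secondary outcomes with the planned time-to-event analysis at 3 and 5 years.

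The cost is two date fields on the existing electronic case report form and slightly more chart abstraction, with no new visits or patients. Recruitment began in January 2016 and is expected to run to December 2031, so most dates can still be captured prospectively. Participants already past their early visits would need dates abstracted from charts.

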## Introduction

### Background and rationale

Retrospective data demonstrates that robotic-assisted thoracoscopic surgery (RTS) provides highly precise instrumentation, 3-dimensional visualization, and a less steep learning curve as compared to video-assisted thoracoscopic surgery (VATS) [1], and RTS may also represent oncological benefit by allowing for improved lymph node dissection [2, 3]. Other potential advantages of RTS-Lobectomy over VATS-Lobectomy are decreased postoperative pain, lower mortality, shorter length of stay in hospital, shorter chest tube duration, and reductions in the incidence of common postoperative pulmonary complications [4–6]. Despite the potential benefits of robotic technology, there are two major barriers against its widespread adoption in thoracic surgery.

The first barrier is the lack of high-quality prospective data. To our knowledge, there are no prospective trials comparing VATS-Lobectomy to RTS-Lobectomy for early-stage lung cancer. In the largest multi-institutional series on RTS-Lobectomy with 325 patients, Park and colleagues reported a median length of stay in hospital of 5 days, 25% perioperative morbidity, 0.3% mortality, and 8% rate of conversion to thoracotomy [3]. Although these results compare favorably to most historical series on VATS-Lobectomy, this trial did not have a VATS-Lobectomy control arm. In a recent database analysis using State Independent Databases of 8 states, a propensity-matched cohort of RTS-Lobectomy was compared to VATS-Lobectomy [6]. Robotic resection was associated with reductions in mortality (0.2% vs 1.1%), length of stay in hospital (5.9 days vs 6.3 days), and overall complication rates (43.8% vs 45.3%) when compared with VATS.

The second major barrier to the widespread adoption of robotic technology in thoracic surgery is the perceived higher cost of RTS pulmonary lobectomy. In a recent trial of the Nationwide Inpatient Sample, it was determined that the incremental additional cost of RTS-Lobectomy over VATS-Lobectomy was $4,708 [7]. This dataset was limited by the absence of patient characteristics, the early learning curve for robotic surgeons, the large proportion of robotic cases being performed in community hospitals with small lobectomy volumes, and the lack of follow-up after discharge from hospital. Data on Health-Related Quality of Life (HRQOL) outcomes were most notably omitted from this trial, hampering any useful conclusion on the cost-effectiveness of RTS-Lobectomy.

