#### Secondary objectives

In Phase A of this trial, we will compare differences in short-term clinical outcomes, and HRQOL outcomes at weeks 3 and 7; and months 6 and 12, which coincide with the intervals of oncological surveillance. We will also compute resource utilization and calculate the incremental cost effectiveness between RTS-Lobectomy and VATS-Lobectomy.

In Phase B of this trial, we will compare the difference in the 5-year survival data between the two arms. We will also compare differences in HRQOL outcomes at months 18 and 24; and years 3, 4, and 5, which coincide with the intervals of oncological surveillance. We will also compute resource utilization and calculate the incremental cost effectiveness between RTS-Lobectomy and VATS-Lobectomy.

RTS-Lobectomy is a new technology that has not been studied extensively yet against VATS-Lobectomy, so equipoise still exists. However, based on preliminary data from our experience and from literature, we hypothesize that for short-term clinical outcomes, RTS-Lobectomy leads to higher quality pathological staging by improved lymphadenectomy, and is associated with shorter duration of chest tube drainage; shorter hospital length of stay; less intraoperative blood loss; lower postoperative analgesia requirements; and less chronic postsurgical pain as compared to those who receive VATS-Lobectomy.

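### All-cause survival is the only long-term cancer outcome: no comparison of recurrence or cause of death is planned, so Phase B cannot say whether the two approaches differ in cancer control

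*Protocol article*

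**What the plan says.** Under Follow-up assessment data collection, the five-year survival data come from a chart review that uses the surgeon's surveillance note, and the content is restricted: "The only survival data that will be collected at five-years is the status of the patient at five years (alive or not").

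Secondary outcomes lists one long-term cancer outcome: "Overall survival, the difference in 5-year survival rate between the two groups will be calculated". Secondary analysis adds: "Time to event analysis models will be used to compare overall survival at 3 years and 5 years between trial arms". Table 3 has an overall survival row with the hypothesis that it improves, and no row for recurrence, disease-free survival or cause of death. Those outcomes are also absent from the Objectives.

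The oncological argument appears in two places. Background and rationale says "RTS may also represent oncological benefit by allowing for improved lymph node dissection". Secondary objectives predicts better lymphadenectomy and pathological staging, as short-term outcomes. The long-term quality-of-life visits are set at times "which coincide with the intervals of oncological surveillance".

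Phase B is sized on survival: "Based on a hypothesized 10% 5-year survival difference between the control arm and the experimental arm", "using the Log-rank test Freedman method with 80% power at a level of significance of 0.05 is 592 patients, with 296 patients per arm".

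**The concern.** The only route to a long-term survival benefit that the article spells out is cancer control through better nodal dissection and staging. The perioperative route it cites is small: database mortality of 0.2% against 1.1%, a gap of 0.9 points, with no deaths in the group's own robotic series and 0% 30-day mortality in its VATS series. Set against a hypothesised 10-point gain at five years, most of the expected effect would have to arise later. The direct long-term consequence of better cancer control is less recurrence, and that is not compared.

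What is at stake is interpretation. A null OS result could mean no difference in cancer control, or a difference masked by deaths from other causes. A positive OS result could reflect cancer control or something else. Recruitment began in January 2016 and is due to end in December 2031, so the last five-year follow-up falls in 2036, about 21 years after the start. If the fields are not collected along the way, the question may not be recoverable then.

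**Working it through.** **Step 1. Reproduce the planned size.** The article gives a 10-point difference, 80% power, alpha 0.05 (two-sided assumed), 1:1 allocation, the Freedman log-rank method and 592 patients. It does not give the control survival rate. Control rates from 50% to 85% were searched in 5-point steps, and only 70% against 80% returns 592:

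- HR = ln 0.80 / ln 0.70 = 0.2231 / 0.3567 = 0.6256
- Deaths = (1.960 + 0.842)² × [(1 + 0.6256) / (1 − 0.6256)]² = 148
- N = 2 × 148 / (2 − 0.70 − 0.80) = 592

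The stated 80% power therefore holds for OS as defined.

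**Step 2. Assumptions for the illustration.** The article gives no cause-of-death split and no recurrence rate, so these inputs are mine: control five-year OS 70%; a share f of the control death hazard due to lung cancer; robotic surgery acts only on cancer events, with hazard ratio HRc; and the same HRc applies to recurrence.

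**Step 3. OS power.** All-cause HR = 1 − f(1 − HRc). Experimental survival S2 = 0.70^HR. Deaths E = 296 × (0.30 + 1 − S2). Power = Φ[√E × (1 − HR)/(1 + HR) − 1.96].

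Worked case, HRc = 0.70 and f = 0.60: HR = 1 − 0.60 × 0.30 = 0.82; S2 = 0.746; E = 296 × 0.554 = 164; power = Φ(12.80 × 0.0989 − 1.96) = Φ(−0.69) = 24%.

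**Step 4. Disease-free survival (DFS) power.** For a control five-year DFS of D, the total cumulative hazard is −ln D, the non-cancer part is (1 − f) × 0.3567, and recurrence is the remainder. DFS HR = (HRc × recurrence + non-cancer) / total. Power uses the same formula with DFS events.

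Worked case, HRc = 0.70, f = 0.60, D = 0.60: total 0.511, non-cancer 0.143, recurrence 0.368; HR = (0.70 × 0.368 + 0.143) / 0.511 = 0.784; 216 events; power 43%.

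| HRc | f | OS HR | OS power | DFS power, D = 55% | D = 60% | D = 65% |
|---|---|---|---|---|---|---|
| 0.70 | 0.5 | 0.85 | 18% | 45% | 36% | 27% |
| 0.70 | 0.6 | 0.82 | 24% | 52% | 43% | 34% |
| 0.70 | 0.7 | 0.79 | 32% | 59% | 50% | 41% |
| 0.60 | 0.5 | 0.80 | 29% | 71% | 59% | 44% |
| 0.60 | 0.6 | 0.76 | 40% | 78% | 68% | 55% |
| 0.60 | 0.7 | 0.72 | 53% | 85% | 77% | 66% |

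**Step 5. Effect needed for the planned 10 points.** If only cancer deaths respond, HRc = [0.6256 − (1 − f)] / f: 0.53 at f = 0.8, 0.47 at 0.7, 0.38 at 0.6 and 0.25 at 0.5.

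In every row DFS has more power than OS, but the gap narrows as control DFS rises.

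**The case against.** Several stronger readings are tempting, and the article does not support them.

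- **That oncological benefit is what motivates the trial.** The article names two barriers, lack of prospective data and perceived cost, and its primary objective is 12-week quality of life. Cancer control is one rationale among several.
- **That this benefit is tested only through OS.** Node count and pathological stage are compared between arms. They are surrogates, but they are the article's own oncological hypotheses. What is missing is a long-term comparison other than OS.
- **That nothing beyond vital status may be abstracted.** The restriction covers survival data at five years. Adverse events are collected to the end of follow-up, and the Study Diary records hospitalisations, tests and procedures. Some recurrences may surface there, but no passage defines or compares them.
- **That OS is heavily diluted or underpowered.** The 10-point effect is set on all-cause survival, and 592 gives 80% power for it. The low figures appear only once a smaller, cancer-only effect is assumed.

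Three further points stand. All-cause survival also captures non-cancer pathways, and the article cites lower mortality and fewer complications as possible benefits. DFS is no cure for low power: at HRc 0.70 it reaches at most 59% in the table, and since the size calculation assumes Stage I patients, the higher control rates are plausible. Finally, providers are not blinded. Recurrence and cause of death taken from the surgeon's notes are open to classification bias, and all-cause death is not.

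**Conclusion.** The point holds as a limitation of the design, not as an internal error. OS is a legitimate endpoint and its stated power reproduces. As written, however, Phase B cannot separate a difference in cancer control from other causes of death, in either direction.

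The loss of power is conditional. At HRc 0.70 with a 50-70% cancer share, OS power is 18-32%, against 27-59% for DFS with control rates of 55-65%. At HRc 0.60 the ranges are 29-53% and 44-85%. All of these rest on an assumed cancer share, hazard ratio and DFS rate, a single hazard ratio for recurrence and cancer death, and no effect on other deaths. The interpretive gap does not depend on those figures.

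The quoted restriction needs revising for a second reason: status at five years alone supplies no death or censoring dates, while Kaplan-Meier, log-rank and Cox analyses and a three-year comparison are planned.

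**What to change.** 1. In Follow-up assessment data collection, replace the alive-or-not restriction. From the surveillance notes already reviewed, record date of death or last contact, cause of death, and date and site of first recurrence (local, regional or distant).
2. In Secondary outcomes and Table 3, add for Phase B: disease-free survival (recurrence or death from any cause, timed from randomisation), and cumulative incidence of recurrence with death without recurrence as a competing event.
3. Keep OS as the sized endpoint. Label the new analyses supportive, and state that recurrence and cause of death come from unblinded surgeons' notes.

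The cost is a few case report form fields, added abstraction time, a minor amendment with matching analysis text, and one or two more secondary outcomes. The classification-bias risk remains and should be acknowledged in reporting. Phase B is still recruiting, so the change can be made now; for patients already enrolled, the same notes would have to be read back.
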